### **Study population/Study subjects**

The study population will primarily consist of HIV-positive men and non-pregnant, HIV-positive women of reproductive age who obtain care at the FACES-supported PSCs in Suba, Kisumu East, Rongo and Migori Districts in Nyanza Province, Kenya. In addition, study subjects will also include clinic staff at the FACES centers included in the study.

### **Inclusion / exclusion criteria for sites**

Eighteen PSCs in Suba, Kisumu East, Rongo and Migori Districts will be selected from existing public health facilities. The existing facilities include sub-district referral hospitals, health centers, and dispensaries. Inclusion in the study will be based on the following criterion: each site must be providing HIV care and treatment services to non-pregnant women of reproductive age. Sites will be excluded if they do not meet the inclusion criterion listed above or if they are already providing integrated comprehensive HIV care and treatment that includes on-site family planning counseling and provision.

## **1. Part I: Baseline data collection (Months 1-3)**

### **1.1. Baseline site-based data collection**

During a period of three months, baseline quantitative data on contraceptive prevalence, contraceptive methods used and pregnancy (including degree to which pregnancy was planned and desired) will be collected as part of routine clinical care at the 18 sites in Suba, Kisumu East, Rongo and Migori Districts. This information will be collected in a standardized clinical encounter form from all HIV-positive women age 18-45 at the time of each visit to the site. Data will also be collected on HIV-positive men age 18-45 regarding condom use, vasectomy and partner's use of other methods. A draft of the questions that will be used to collect the site-based data is included in Appendix A.

### **1.2. Baseline knowledge, attitudes and practices (KAP) survey of female and male clients**

Also during this three-month period, a convenience sample of approximately 28 female patients and 28 male patients will be recruited from each of the 18 sites (N=488 female and 488 male patients) to complete a questionnaire regarding knowledge, attitudes and practices (KAP) related to family planning. The purpose of the KAP survey is both to 1) measure the satisfaction with the family planning services offered at the HIV care and treatment clinic, 2) provide information that will be used to design the family planning integration intervention and improve family planning provision, and 3) provide a baseline measure of KAP that will be compared to follow-up surveys at the end of the study.

The survey will be administered face-to-face by an interviewer in the respondent's preferred language in a private area of the centre.

The inclusion criteria for the client KAP survey will be:

- 1) HIV-positive woman or man obtaining care at the FACES site
- 2) Not currently pregnant (if female)
- 3) Age 18 to 45 years old if female; age 18+ if male
- 4) Willing and able to give informed consent

Clients will be excluded if they do not meet the inclusion criteria listed above. Some of the topics included in the KAP survey will be: familiarity with contraceptive methods; prior and current contraceptive use; partner's role in contraceptive decision-making; interest in preventing pregnancy in the future; and acceptability of and satisfaction with currently-offered family planning services at the site. The survey will be adapted from the Demographic and Health Survey modules on contraception, marriage and sexuality, and fertility preferences (see Appendix B1-1 for women's survey and Appendix B1-2 for men's survey). We will train our interviewers to provide referrals for women who need counseling or support services to a local women's non-governmental organization (NGO) working in Migori District, the Women's Action Forum for Networking (WAFNET). These referrals will be provided to women who report domestic abuse (psychological, physical, or sexual) or other negative events during the interviews. Participants will be reimbursed a maximum of USD\$3 (approximately 200 Kenyan Shillings at current exchange rate) for transport.

### **1.3. Baseline open-ended interviews with female and male clients**

During the three-month baseline period, we will perform 30 open-ended interviews with female patients recruited from the 18 PSC sites. We will also perform 30 open-ended interviews with male patients recruited from the same sites. These patients will be a subset of those participating in the KAP questionnaire. The purpose of these interviews will be to obtain qualitative information about their reproductive intentions and their

perceived barriers to obtaining and using effective contraception, information that cannot be easily obtained using the survey methodology. These data will be used to design the family planning integration intervention. The final version of the interview guides will be submitted to the IRB prior to initiating data collection.

A convenience sample of 30 women and 30 men will be invited to participate in the open-ended interview. The open-ended interview will be performed in the respondent's preferred language in a private area of the centre and will take approximately 30 minutes to complete. The inclusion criteria will be:

- 1) HIV-positive woman or man obtaining care at the PSC site
- 2) Not currently pregnant (if woman)
- 3) Age 18 to 45 years old if female, age 18+ if male
- 4) Has not received vasectomy or tubal ligation
- 5) Willing and able to give informed consent

Subjects will be reimbursed a maximum of USD\$3 (approximately 200 Kenyan Shillings at current exchange rate) for transport.

All interviews will be tape recorded (if the woman gives informed consent), transcribed, translated to English, and a content analysis will be performed using the qualitative software ATLAS.ti.

#### **1.4. Baseline survey with clinic staff at PSC sites**

During the three-month baseline period, we will also administer a survey to approximately 30-45 clinic staff at HIV care and treatment sites, including doctors, nurses, clinical officers and peer counselors (convenience sample of approximately 3-4 at each site). The purpose of the KAP survey is both to 1) provide information that will be used to design the family planning integration intervention in the subsequent study, and 2) provide a baseline measure of KAP that will be compared to follow-up surveys of the same clinic providers at the end of the study. The final version of the survey will be submitted to the IRB prior to initiating data collection.

The survey will be administered by an interviewer in the respondent's preferred language in a private area of the centre. Inclusion criteria for the clinic staff survey will be: 1) clinic staff at the FACES-supported PSC site with direct patient contact, and 2) willing and able to give informed consent. Clinic staff will be excluded if they do not meet the inclusion criteria listed above. Some of the topics included in the survey will be knowledge of contraceptive methods and appropriate counseling, prior experience providing methods and interest in playing a more active role in contraception provision. Open-ended questions will attempt to obtain qualitative information about the perceived barriers to providing contraception in the sites. The responses to these open-ended questions that will be tape recorded (if the participant gives his/her consent), transcribed, translated to English (if interview not performed in English), and a content analysis will be performed using the qualitative software ATLAS.ti. Clinic staff will be reimbursed with a book voucher worth approximately USD\$5 (approximately 350 Kenyan Shillings at current exchange rate) for participating in the survey.

## **2. Part II: Intervention design and implementation (Months 4-6)**

The study will be conducted as a cluster-randomized trial. Eighteen clinical sites in the Suba, Kisumu East, Rongo and Migori Districts will be randomized to a family planning intervention or to control. Sites will be grouped into strata based on the overall patient

volume and differences in the structure of family planning provision. The randomization scheme will be generated using STATA statistical software. Below we briefly outline the design and implementation of the intervention.

## 2.1. Intervention design

The information gathered during the baseline data collection period will serve to inform the ultimate design of the family planning intervention. During the Hormonal Contraception and HIV: Science and Policy Africa Regional Meeting in Nairobi in 2005, one of the important areas for further research identified was a “better understanding of how effectively to promote dual protection, especially optimal counseling processes and techniques.[25]” Additionally, a needs assessment performed in Uganda[26] prior to integrating family planning into HIV services there identified several issues, among them were: the need to include men in family planning education/counseling, fear of side effects of contraception among rural HIV-infected individuals; lack of family planning training among health care providers; and concern among some health care providers that promoting contraception will encourage HIV infected clients to have sex. Our intervention will take into account the areas identified in the Nairobi meeting and in the Uganda needs assessment in addition to the Nyanza-specific needs assessment that will be conducted during Part 1 of the project. In planning our intervention, we will aim to create an optimal way to integrate family planning counseling, family planning method provision and dual method promotion into HIV care and treatment services.

The intervention to be designed will include four major components of care: patient education; family planning counseling; method provision, including risk assessment; and contraception follow-up. The details of the intervention will greatly depend on the information gathered during the qualitative interviews with clients and clinicians, as well as the results of the KAP surveys. With these results, the research team will be able to tailor the design of the intervention to meet the needs of patients and providers in the Nyanza Province. Particular attention will be paid to results regarding: myths about and barriers to family planning; methods preferred by patients; feasibility of providing long-acting methods such as implants and intrauterine contraception; preference for types of locations and clinicians from whom patients feel most comfortable receiving family planning; and clinicians’ concerns regarding assessments of family planning needs and provision of methods. With regards to method provision, the intervention will incorporate the Kenyan *Family Planning Guidelines For Service Providers* written and revised by the Kenyan Ministry of Health’s Division of Reproductive Health in 2005[27]. The integration model will aim to address needs identified during the baseline data collection period and, as appropriate, will be loosely modeled after existing family planning and HIV care integration programs in Uganda, Zambia, and Zimbabwe [28].

Specifically, the intervention will consist of:

- Patient Education:
  - Group and individual education sessions geared toward:
    - Explaining importance of dual method protection: differentiating the importance of condom use for prevention of STI transmission from the importance of family planning for pregnancy prevention
    - Explaining the different methods available (pills, injections, implants, intrauterine devices, sterilization), how they work, and potential side effects associated

- Tailored client education materials focusing on available methods, importance of contraception and dual method use, and side effects of different methods will be created in the forms of low literacy pamphlets, flip charts, and posters.
- Family planning counseling:
  - Extensive provider and health counselor training in family planning including:
    - How to incorporate family planning counseling into HIV enrollment and follow-up visit (inquiring at each visit as to patient's contraceptive needs, questions, etc.)
    - The importance of contraception for pregnancy prevention
    - Side effects of contraception
    - Risks of contraception
    - The importance of dual method use to prevent transmission of STI's
    - The significance of preventing unintended pregnancies with regards to prevention of maternal-to-child HIV transmission
    - Training on individual and group family planning counseling techniques, including an assessment of patients' contraceptive needs/desires in the context of their lives and health situations
    - Education on contraception options, contraceptive risks and side effects, and prescription and dispensing of contraception
    - Promotion of male partner involvement in family planning education and choices
- Method Provision:
  - Contraception will be prescribed directly by HIV care and treatment program clinicians. Commodities will be obtained through the normal Ministry of Health procurement process.
  - Education for providers regarding individual patient risk assessment based on client's health status and current co-morbidities
    - Examples:
      - Risk of thrombosis for patients who have a history of thrombosis, who smoke, etc.
      - Contraceptive interactions with ART medications, antibiotics, anti-tuberculosis medications, anti-seizure medications, etc.
  - Education for providers regarding dosing of hormonal contraception, timing of initiation (including education about and promotion of "Quick Start" methodology), and interval follow-up and repeat dosing (for injectables)
  - Training on intrauterine contraception and implant insertion at clinics where provision of these methods is feasible.
- Contraception Follow-up
  - Training of providers regarding method-specific follow-up:
    - appropriate timing of follow-up
    - questions about side effects, method satisfaction
    - follow-up physical exam (if method appropriate)
  - Integration of contraception follow-up into routine HIV follow-up appointments

## 2.2 Intervention implementation

After the intervention is fully designed, it will be implemented at twelve “intervention” FACES-supported PSC’s using a model that will ultimately include integrating HIV and FP services in all 18 sites. Implementing the intervention will consist of:

- Training clinic staff in family planning counseling and method provision
- Introducing family planning assessments into all clinic visits via incorporating inquiries as to family planning needs on all medical forms, thereby prompting provider questioning
- Introducing new client counseling sessions and education materials into the PSC care infrastructure
- Devising a system of procuring, inventorying and dispensing contraceptive methods, including at the very least condoms, oral contraceptives and injectables. At sites where it is feasible, IUDs and implants will also be made available. When a method is not available at the site (such as in the case of surgical sterilization), clients will be referred to nearby centers that offer the method.

At both the intervention and control sites, a brief family planning module will be integrated into the standardized clinic encounter form that is used at each client visit. This module will prompt the clinician to ask if the client is currently using contraception and his or her fertility intentions. Simply put, if the client is using a method, the provider will be ask if he or she is interested in changing the method; if the client is not using a method and does not desire pregnancy, the provider will be ask if he or she is interested in starting a method.

- At “intervention” sites clients will then be extensively counseled about contraception and will be provided any needed contraceptive methods on site.
- At “control” sites, clients will be provided with contraceptive services through the centers’ standard mechanisms, which generally involve referral to an affiliated family planning program that may or may not be on-site.

Prior to implementation of our intervention, we will resubmit the protocol for review at SSC/ERC for review of the final design of any educational materials developed.

### **3. Part III: Post-intervention data collection (Months 7-15)**

#### **3.1. Post-intervention site-based data collection**

Over the following nine months, data on contraceptive prevalence, contraceptive methods used and pregnancy (including degree to which pregnancy was planned and desired) will be collected, as part of routine care, at the 18 sites (twelve intervention and six control sites) among women age 18-45 and men age 18 and older. Data will also be collected on whether contraceptive counseling was performed at each clinic visit. This information will be collected in the standardized clinic encounter form from all HIV-positive women and men at the time of each visit to the site. At each of the sites, a random sample of 10-15% of all charts will be reviewed during the post-intervention period to determine if the family planning module of the clinical encounter form is being filled out. A draft of the questions that will be used to collect the site-based data is included in Appendix A.

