### **Preliminary data**

In 2006, we performed an internal service provision improvement evaluation of the reproductive health services at FACES clinics[24]. The evaluation consisted of 24 structured observations of all types of client interactions, including Voluntary Counseling and Testing (VCT), HIV (peer) education, adherence counseling, enrollment visits, clinical and non-clinical follow-up visits, and family counseling sessions.

Several barriers to effective reproductive healthcare were identified: environmental barriers (related to space, examining equipment, contraceptive methods available, cultural discomfort, technical discomfort with gynecologic exams); lack of inclusion of reproductive health history into enrollment and follow-up visits; lack of inclusion of family planning counseling/care into routine clinic visits; long intervals between client request for family planning and actual method initiation; and lack of family planning counseling training/experience among clinic staff.

The evaluation revealed that only 20% of the observed clinical encounters involved any family planning (FP) counseling and only 16% of clinical encounters involved spontaneous, provider-initiated FP information. The content of the FP counseling varied greatly. Despite a space on the intake form for the date of the last menstrual period, frequently when answers of greater than one month were given, an evaluation for pregnancy was not performed. This inadequate response to delayed menses raises the concern of the occurrence of unintended pregnancies, potential teratogenicity of HIV medication when pregnancy is not detected, and missed opportunities for early referral to antenatal care. Additionally, despite prompts on the clinical intake forms, providers were observed to inquire about sexual activity and contraception use only approximately 30% of the time. Only three of the observed clinical encounters resulted in steps towards contraception initiation and only one of the 24 observed clinical encounters involved any discussion of screening for risks involved with different contraceptive methods.

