  - a. The primary outcome upon which we based our sample size calculation is contraceptive prevalence. According to the 2003 Kenya Demographic and Health Survey, approximately 22% of women in a union in Nyanza Province use a modern contraceptive method. This level of contraceptive prevalence is similar to that seen among clients at the FACES sites. We would like to be able to detect a 8% rise in contraceptive prevalence to 30%.
- 3. Assumptions
  - a. Two-sided alpha of 0.05
  - b. Power of 0.8
  - c. Intra-cluster Correlation Coefficient of 0.01
- 4. Sample size.
  - a. Using these estimates, the needed sample size is approximately 140 women at each of the 18 sites, for a total sample of 2,520 women.
  - b. We plan to initially recruit a similar number, 2,520, of male clients, however our primary outcome for men will be the proportion of male clients who report they or their partner are interested in starting a new FP method after receiving FP counseling during their visit. In order to accurately calculate this sample size, baseline data is needed to estimate the baseline proportion of male clients who would express interest in starting a new FP method. Thus, after the baseline data collection phase a more accurate sample size for male clients will be calculated.

**KAP surveys.** Because the largest sample sizes are required for expected proportions nearer to 0.5 than to 0 or 1, we will take the worst-case scenario and assume that for each individual question on the survey approximately half of the participants will answer correctly. We hypothesize that people in the intervention sites will be more knowledgeable after the intervention at the end of the study, so we would like to test for at least a ten percentage point difference in correct answers among patients in the intervention sites (~60% correct) compared to patients in the comparison sites (~50% correct), as well as a 10% increase in correct answers among patients in the intervention sites compared to the baseline results. For a one-sided test of two proportions using two samples, power of 0.8, and an alpha level of 0.05, the required sample size is 325 patients from the intervention sites and 163 patients from the comparison sites for both men (N=488) and women (N=488).

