## **LIMITATIONS**

### **Potential Design Pitfalls**

Non comparable sites: Government facilities in Suba, Kisumu East, Rongo and Migori Districts provide varying levels of care from basic outpatient dispensaries with minimal staff and facilities and services, to the district hospital with comprehensive diagnostic and treatment services including inpatient and outpatient facilities. Comparisons of facilities offering different levels of care would likely introduce confounding factors into the study outcomes. To avoid this potential confounding influence, we will perform an initial assessment of each of the possible sites and divide them into similar groups according to the number of clients served, the type of facility, the geographical location, and the type of HIV and family planning services currently available on site. We will group the sites into two strata based on this information; six intervention and three

control sites will be selected from each of the two strata. In addition, intra-cluster correlation is factored into our data analysis plan (see above section on statistical/analysis plan).

Non-uniform protocol implementation: We will train all health staff and paramedical staff in the standard operating procedure for each HIV care and treatment clinic, including the standard operating procedures for integration or non-integration of family planning services with HIV care and treatment. However, as in all settings, it is impossible to control for individual staff motivation. Therefore, it is possible that some sites will follow the protocol more stringently than others and that some sites will recruit patients more enthusiastically than others. With a randomized design the potential confounder of staff motivation should be evenly distributed in both the intervention and the control arms, thereby minimizing the problem of confounding influences.

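### Contraceptive use is recorded by unmasked treating clinicians, and the protocol does not secure equal completion of the form in the two arms

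*Protocol*

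**What the plan says.** - **Source of the outcome.** The Endpoints section takes contraceptive prevalence from clinic encounter forms. Section 2.2 places the same family planning module on the form at intervention and control sites and has the clinician ask about current use. No masked or independent ascertainment of this outcome is described.
- **Training.** Section 2.1 lists, within the intervention's provider training, "inquiring at each visit as to" the patient's contraceptive needs and questions. The Limitations section says all staff are trained in their own clinic's procedures, "including the standard operating procedures for integration or non-integration of family planning services". It does not say that control staff are trained to complete the module.
- **Evidence on prompts.** Under Preliminary data, despite prompts on the intake forms, "providers were observed to inquire about sexual activity and contraception use only approximately 30% of the time".
- **Check on completion.** Section 3.1 says that at each site "a random sample of 10-15% of all charts will be reviewed during the post-intervention period to determine if the family planning module" is being filled out. It states no comparison by arm, no threshold and no consequence.
- **Protocol's view of uneven adherence.** The Limitations section accepts that some sites will follow the protocol more closely than others, then says: "With a randomized design the potential confounder of staff motivation should be evenly distributed in both the intervention and the control arms".

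**The concern.** A woman's contraceptive use reaches the primary analysis only if a clinician asks and writes the answer down. One arm is trained to raise contraception at every visit. The other has the same printed prompt but no stated training in using it. In the protocol's own evaluation a prompt alone was weak.

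The randomisation argument does not cover this. Randomisation balances, in expectation, the motivation that staff bring to the trial. It does not balance asking and recording that arm-specific training changes after allocation. If completeness differs by arm, part of the between-arm difference may be a difference in measurement. A real rise in use because women were asked and counselled is a different matter: that is intervention effect, not bias.

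**Working it through.** **Inputs from the protocol.** Baseline prevalence comes from the sample size section ("approximately 22% of women in a union in Nyanza Province use a modern contraceptive method"). The target is 30%, a rise of 8 points, with 12 intervention and 6 control sites, 140 women per site, ICC 0.01, "Two-sided alpha of 0.05" and power 0.8. Completion rates by arm are not given; every rate below except the 30% asking rate is an assumption.

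**The plan's own figure.** For 22% against 30% at 2:1, two-sided 0.05 and 80% power, the individually randomised requirement is 358 control women, 1,074 in all. The design effect is 1 + (140 − 1) × 0.01 = 2.39. Then 1,074 × 2.39 ≈ 2,567, against the stated 2,520 (power 0.793 at 2,520). The sample size reproduces and is not in question here.

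**Case A: blanks count as non-use.** Observed prevalence = true prevalence × completion. With no true effect, false difference = prevalence × completion gap.

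| True use, both arms | Completion, intervention v control | Observed | False difference |
|---|---|---|---|
| 22% | 95% v 90% | 20.9% v 19.8% | 1.1 points |
| 22% | 95% v 80% | 20.9% v 17.6% | 3.3 points |
| 22% | 95% v 70% | 20.9% v 15.4% | 5.5 points |
| 22% | 90% v 30% | 19.8% v 6.6% | 13.2 points |

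- Gap needed for a false 8 points: 0.08 / 0.22 = 36 points, or 0.08 / 0.30 = 27 points if true use is 30%.
- False rejection at 95% v 80%: SE = √(2.39 × [0.209 × 0.791 / 1,680 + 0.176 × 0.824 / 840]) = 0.0255. The ratio 0.033 / 0.0255 is 1.30, so a nominal 5% test rejects about 25% of the time.
- Hiding a true 30% v 22% would need intervention completion at 0.22 / 0.30 = 73% of control completion, the less likely direction.

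**Case B: blanks are dropped.** Observed prevalence = P·a / (P·a + (1 − P)·b), where a and b are the chances that a user and a non-user are recorded. If a = b, observed equals true whatever the completion rate. For 22% to read as 30%, a/b must be (0.30/0.70) / (0.22/0.78) = 1.52, for example 95% v 62.5%.

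**Repeat visits.** The module is used at every visit over nine months. Suppose any recorded visit supplies a woman's status and visits are independent (both assumptions). Then 90% v 30% per visit becomes 1 − 0.1³ = 99.9% v 1 − 0.7³ = 65.7% over three visits, and about 100% v 1 − 0.7⁶ = 88.2% over six. The 13.2 points falls to about 7.5 and 2.6. Correlated visits would shrink it less.

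**What the planned review could show.** If charts are those of 140 women per site, 10–15% is 14–21 charts. At 80% completion (assumed) the 95% half-width is 17–21 points per site. For the arm difference it is 1.96 × √(0.16/(6n) + 0.16/(12n)), or 8.6–10.5 points for n = 21 and 14, before clustering. A gap of 27–36 points would be visible if the arms were compared.

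**The case against.** A reader might infer that asking is trained only in the intervention arm, that completion will differ by arm, and that this can create or hide the whole planned effect. The documents do not support that.

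- The training item in section 2.1 concerns contraceptive needs, that is, counselling. The item on current use is prompted by the same module in both arms. The data are collected on a standardised form at all 18 sites for three months before randomisation, and all staff receive procedure training.
- The chart review is not the only control. The data management section gives the study coordinator regular site visits, data checking and quality control, and has research assistants abstract the records. The review runs at each site, so comparing arms needs no new data.
- The 30% figure comes from 24 mixed encounters, including testing and peer education sessions. The protocol itself notes the small sample and non-standardised method. It cannot stand as a forecast of control-site completion.
- The large false differences need blanks to count as non-use. The protocol promises a detailed analysis plan, which is not at hand, so the absence of a blank-handling rule is not a finding.
- The sentence on motivation concerns following the protocol and recruiting, and pre-existing motivation is indeed balanced in expectation.

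All of this limits the size of the point. What remains is that no text gives control staff training in completing the module, the general quality-control duties set no completeness standard, and the randomisation sentence offers reassurance that does not extend to recording behaviour changed by training.

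**Conclusion.** The concern holds as a risk, not as an established difference. Ascertainment of the primary outcome is open to influence by arm, and the protocol has a review in place that could detect this but does not say it will be read by arm or acted on.

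The size depends on assumed completion rates and on a rule for blanks that is not shown. With blanks as non-use and 22% true use, a 15-point gap costs about 3.3 points and a 5-point gap about 1.1; only a gap of about 36 points (27 at 30% use) would manufacture the full 8. Repeat visits would reduce woman-level gaps. With blanks dropped, differential completion alone gives no bias; recording must also depend on use. The protocol should be changed because even a moderate gap could inflate false rejection and because answers never sought cannot be recovered in analysis.

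**What to change.** 1. Within the procedure training already planned for all staff, give identical training in completing the module at all 18 sites, separate from the counselling training.
2. Run the existing 10–15% chart review in the baseline period as well, so that site differences present before allocation can be told from those that follow it. Tabulate completeness by site and arm during data collection. State in advance a completeness threshold and a between-arm gap that trigger refresher training in form completion. A gap of 10 points is about the smallest the review can resolve, and under blanks as non-use it corresponds to 0.22 × 10 = 2.2 false points.
3. Reword the Limitations paragraph to say that randomisation balances pre-existing staff motivation but does not protect against recording that differs because of the arm.
4. Optionally, report current use by arm from the interviewer-administered end-of-study KAP survey as a coarse supportive check. It is a convenience sample of about 28 women per site (336 v 168). At 22% use the half-width is 1.96 × √(0.22 × 0.78 × [1/336 + 1/168]) = 7.7 points, or 8.6 with ICC 0.01, so it cannot confirm or refute the form-based result.

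Cost: protocol wording, a short item in planned training, and an extension of a planned review. The downside is some added monitoring work, and form training may slightly sharpen control practice.
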